## Abstract

**Background:**

Termination of pregnancy for fetal abnormalities (TOPFA) represents a significant global healthcare challenge. In China, the occurrence of fetal abnormalities is notably high. TOPFA is a devastating traumatic event for parents and families. Parents frequently encounter psychological issues and negative emotions such as depression, anxiety, prolonged grief, feelings of inadequacy, persistent guilt, and symptoms of post-traumatic stress disorder (PTSD).

**Methods/design:**

This prospective, randomized controlled trial aims to assess the feasibility and impact of a mindfulness-based, couple-centered intervention (MBCI) on anxiety, depression, mindfulness level, and family support among bereaved parents. The study will enroll 124 couples experiencing TOPFA. Participants will be randomly assigned to either the intervention group (receiving MBCI in addition to routine psychological care) or the control group (receiving only routine psychological care). Data will be collected at three time points: baseline, post-intervention and 42 days postpartum. Additionally, participants are expected to complete a weekly mindfulness exercise feedback form. Semi-structured, in-depth interviews with the intervention group will be conducted post-intervention and 42 days postpartum.

**Discussion:**

This RCT aims to investigate the effectiveness of a couple-centered mindfulness intervention on the psychological well-being of parents experiencing TOPFA. If effective, this intervention could serve as a complement to routine psychological care, aiding in the physical and mental recovery of women and their families.

## Introduction

Fetal abnormalities encompass congenital malformations and stillbirths. In 2017, worldwide, 280,000 newborns died within 28 days of birth from congenital malformations, 14,000 of which were in China [1]. According to 2023 WHO data, approximately 1.9 million stillbirths and 2.3 million neonatal deaths occur globally each year [2].

The occurrence of sudden fetal anomalies or stillbirth during pregnancy is a significant traumatic event for pregnant women and their families, leading to intense and prolonged grief and destructive psychosocial issues [3, 4]. Approximately 80% of women who experience perinatal loss have symptoms of grief or bereavement [5], about 50% of women experience grief symptoms that last longer than 4 years [6], and often accompanied by comorbidities such as post-traumatic stress disorder (PTSD), anxiety, depression, sleep disturbances, and eating disorders [6, 7]. Psychological surveys of parents who underwent terminations of pregnancy for fetal abnormalities (TOPFA) showed that the prevalence of anxiety was 24.3% for mothers and 19.5% for fathers, depression was 50.3% for mothers and 24.9% for fathers, and PTSD was 21.3% for mothers and 20.1% for fathers, with significant correlations between anxiety, depression, and PTSD levels for both mothers and fathers [8, 9], indicating that both mothers and fathers experience significant PTSD, anxiety, and depression, and their negative emotions affect each other. Furthermore, stillbirth is an important risk factor for anxiety and depression during subsequent pregnancies and the postpartum period [10, 11]. Therefore, effective psychological interventions are urgently needed to provide synchronous interventions for both mothers and fathers [8, 9]. Qualitative interviews with mothers who experienced TOPFA during the postpartum period revealed that negative psychological experiences coexist with positive psychological experiences in this population, and their caregiving needs exhibit diverse characteristics [12], as shown in Fig. 1.

**Fig. 1 Fig1:**
[figure not shown]
Psychological Experience of Women with TOPFA during Postpartum Period

Currently, psychological care for parents undergoing TOPFA primarily consists of perinatal grief counseling, psychological counseling and treatment, and support from family, peers, groups, and associations [13–17]. The Swedish National Infant Foundation (SNIF) established a “self-help” group support model, offering a platform for parents to communicate and express their grief, thereby aiding them in adjusting better to their loss [18] Kersting et al. [19] conducted a five-week internet-based cognitive-behavioral intervention that effectively reduced symptoms of grief, depression, and PTSD in bereaved mothers. In the UK, charitable organizations like Antenatal Results and Choices (ARC) [20] and Stillbirth & Neonatal Death Society (Sands) offer social support and long-term follow-up for this group.

Mindfulness intervention, a novel psychological therapy, is widely used internationally for preventing or treating various psychological issues. Scholars have also applied mindfulness intervention to the prevention and treatment of anxiety and depression among pregnant and postpartum women. Lisa Roberts et al. [21] conducted a five-week localized mindfulness intervention for mothers who experienced stillbirth, showing that it reduced symptoms of perinatal grief, anxiety, and depression. Jennifer Huberty et al. [22] conducted a 12-week online mindfulness yoga intervention for mothers who experienced stillbirth, which effectively alleviated symptoms of PTSD, grief, and depression. Thieleman and Cacciatore [23] explored a grief-focused mindfulness-based retreat’s effectiveness on psychological distress and well-being in bereaved parents, finding it decreased trauma responses and distress. Chen et al. [24] and Zeng et al. [25] conducted mindfulness-based intervention studies focusing on four intensive short-term mindfulness training sessions during hospitalization, complemented by three weeks of home self-practice after discharge. These interventions effectively increased mindfulness levels and alleviated anxiety and depression in mothers.

Fathers experiencing TOPFA also indirectly suffer from the grief and psychological trauma associated with TOPFA. Negative psychological effects mutually influence both mothers and fathers [9], underscoring the necessity of including fathers in psychological interventions to promote synchronous recovery for both parents experiencing TOPFA. However, previous psychological interventions rarely included fathers, overlooking the importance of paternal psychology and its impact on maternal psychological health. Therefore, this study included both mothers and fathers who experienced TOPFA as research subjects simultaneously. This study aims to assess the feasibility and effects of a mindfulness-based, couple-centered intervention (MBCI) on anxiety, depression, mindfulness levels, and family support among bereaved parents.

## Methods

### Study design

This trial is randomized, involving parallel groups, and is controlled. The trial has been registered with the Chinese Clinical Trial Registry (ChiCTR2100054164). The study protocol follows the Standard Protocol Items: Recommendations for Interventional Trials (SPIRIT) checklist.

## Setting and recruitment

Screening and enrollment of participants will occur on the admission day. This study conducted at the Women’s Hospital School of Medicine, Zhejiang University. This study aims to enroll 124 couples experiencing TOPFA, with 62 couples in both the intervention and control groups. The study’s recruitment phase was initiated on March 21, 2022, and the data collection process is projected to be finalized by October 31, 2025. The study’s flow chart is presented in Fig. 2.

**Fig. 2 Fig2:**
[figure not shown]
Flow diagram of enrollment, interventions, and assessment. T0: Baseline; T6: Post-intervention; T7: 42 days postpartum

## Eligibility criteria

The inclusion criteria include: a diagnosis of fetal abnormality confirmed by Zhejiang Provincial Prenatal Diagnosis Center and a decision to terminate the pregnancy due to the fetal abnormality after > 14 gestational weeks. Couples must be over 18 years old, have no prior participation in mindfulness-related psychological interventions or other scientific research, be proficient in using WeChat, willing to accept online interventions via WeChat, and both spouses must voluntarily participate and provide signed informed consent. The exclusion criteria include: a history of psychosomatic diseases; intellectual disabilities, illiteracy, or an inability to understand the intervention and assessment content; development of severe psychosomatic issues during the study, preventing participation; voluntary withdrawal or loss of contact during the study; incomplete research questionnaires or missing items.

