## Randomization

After signing the informed consent, participants will be randomly assigned to obstetric wards 2 through 7. To prevent cross-contamination that could impact intervention effectiveness, those in wards 2 to 4 will be assigned to the intervention group, and those in wards 5 to 7 will be part of the control group. The intervention group will receive MBCI in addition to routine psychological care, whereas the control group will only receive routine psychological care.

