### Statistical analysis

#### Sample size

To calculate the necessary sample size, the formula N1 = N2 = 2[(Zα + Zβ)S/δ]^2^ is used. Based on results from previous mindfulness intervention studies [21] on mental health symptoms, we derived values: S = 0.64, δ = 0.41, α = 0.05, and β = 0.10. Applying these values, the estimated total sample size is 104. Accounting for a 20% attrition rate and sampling error, the estimated sample size for each of the intervention and control groups is 62.

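### The exclusion criteria include events that arise wholly or largely after allocation, so followed as written they remove randomised couples from the comparison

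*Protocol article*

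**What the plan says.** In the protocol article, Eligibility criteria, the list of exclusions starts with conditions that can be checked at screening. It then continues with three of another kind: "development of severe psychosomatic issues during the study, preventing participation; voluntary withdrawal or loss of contact during the study; incomplete research questionnaires or missing items".

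The timing is given elsewhere:

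- Setting and recruitment: "Screening and enrollment of participants will occur on the admission day".
- Randomization: "After signing the informed consent, participants will be randomly assigned to obstetric wards 2 through 7". The ward decides the arm.
- Assessments, Table 2: eligibility screen, consent and allocation are all at T0. GAD-7, PHQ-9, Family APGAR and FFMQ are completed at T0, T6 and T7, so two of the three outcome visits follow allocation.

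The Sample size section deals with losses by enrolling more couples: "Accounting for a 20% attrition rate and sampling error, the estimated sample size for each of the intervention and control groups is 62". The Plan of data analysis specifies repeated measures ANOVA or generalized estimating equations (GEE). It names no analysis population and does not say that couples meeting the three criteria stay in the comparison.

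**The concern.** An exclusion criterion normally rests on what is known before allocation. A rule triggered by what happens afterwards selects among randomised couples, and the two arms need not be selected alike.

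The three rules differ in how close they come to the outcome. The first concerns severe psychosomatic issues that stop participation, a state near to the anxiety and depression that the trial measures. Withdrawal, loss of contact and blank items are not outcomes, but they are plausibly related to outcome and to arm: the Discussion states that there is no blinding, and only the intervention arm has six sessions of 1.5 to 2 hours.

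At stake is the randomised comparison on all four scales. There is also a practical cost. A rule that discards a couple for an unanswered item could remove more couples than the sample size allows for.

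**Working it through.** **1. The plan's own figure.** Inputs from Sample size: S = 0.64, δ = 0.41, α = 0.05, β = 0.10. Taken two-sided, 2[(1.960 + 1.282) × 0.64/0.41]² = 51.2, rounded up to 52 per arm and 104 in total. This matches the text. The 62 per arm corresponds to 51.2 × 1.2 = 61.4, rounded up. The planning effect is 0.41/0.64 = 0.64 SD.

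**2. When each rule can act.** Screening, consent and allocation share T0.

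- Severe psychosomatic issues during the study: after allocation.
- Withdrawal or loss of contact during the study: after allocation.
- Incomplete questionnaires or missing items: no time limit is given, so T0, T6 and T7 are all covered. Two of these three visits follow allocation.

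**3. Possible bias (hypothetical).** The removal shares are assumptions; the document gives none by arm or reason. Take normal scores, no true effect, and removal of the worst-scoring share q. The retained mean is −φ(c)/(1 − q) in SD units, where c is the (1 − q) quantile.

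- q = 5%: −0.109. q = 10%: −0.195.
- 10% v 5%: difference 0.086 SD, and 0.086/0.64 = 13% of the planning effect.
- 10% v 0%: difference 0.195 SD, or 30% of the planning effect.
- Equal shares: difference 0.

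These figures assume that exactly the worst scorers go. A simulation of t-tests with 62 per arm and no true effect (20,000 runs per setting) shows how much this matters. With 20% v 10% removed, type I error at a nominal 5% is 16.4% if removal follows the outcome fully, and 6.7% if the variable driving removal correlates 0.5 with the outcome. With 20% removed in both arms it is about 5%.

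**4. Reach of the missing-item rule (hypothetical).** GAD-7 has 7 items, PHQ-9 has 9 and FFMQ has 39. Family APGAR is taken as 5, an assumption from its five dimensions. That gives 60 items × 2 partners × 3 visits = 360 responses per couple. Assume that one blank excludes the couple and that omissions are independent at rate p. The share excluded is 1 − (1 − p)³⁶⁰:

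- p = 0.05%: 16%
- p = 0.1%: 30%
- p = 0.2%: 51%

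**5. Power.** With all 62 per arm analysed, two-sided power is 94.6%. With 20% removed, 62 × 0.8 = 49.6 per arm and power is 88.7% to 89.3% (49 and 50 per arm), just under the planned 90%. At that level of loss the main harm is bias rather than power.

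**The case against.** The strongest defence is that these are discontinuation criteria filed in the wrong place. The article nowhere says in so many words that the couples leave the analysis, and an analysis set and missing-data rules may sit in a fuller document. Part of this stands: the lack of a detailed missing-data plan in an article is no finding, and this point rests only on the criteria that are stated. But the defence does not cover the third criterion. A blank item is no reason to stop taking part, so that rule works only as a rule for discarding data. Nothing in the article cancels any of the three.

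Several stronger readings are tempting, and the document does not support them:

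- *All three rules drop couples on their outcome.* Only the first is close to the outcome. It is limited to issues that prevent participation and is not a GAD-7 or PHQ-9 threshold.
- *All three act only after randomisation.* The missing-item rule can also act on the T0 questionnaires.
- *Weekly feedback forms burden only the intervention arm.* The form's content suggests this, but the abstract and Assessments assign it to participants and couples generally, and its row in Table 2 names no arm. Only the six sessions are stated to be specific to one arm.
- *The feasibility aim is lost because retention becomes 100% by construction.* The abstract says that the trial "aims to assess the feasibility and impact of a mindfulness-based, couple-centered intervention". Leaving couples out of a score comparison does not prevent losses from being counted, and interviews and feedback forms also inform feasibility.

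The magnitudes are also open to challenge. The text does not say whether a blank item excludes the partner or the couple. Omissions cluster within people, so fewer couples would be lost at the same rate than under independence.

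**Conclusion.** The point holds as a fault in a stated rule: two post-allocation events, and a third that acts largely after allocation, are grounds for exclusion, and nothing in the article keeps those couples in the comparison. It should be corrected before any comparison by arm.

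The direction and size of the bias cannot be derived from the document. The shifts of about 0.09 SD (10% v 5%) and 0.19 SD (10% v 0%) show what unequal, fully outcome-related removal could do against a planning effect of 0.64 SD. They do not predict what will happen, and equal removal with no true effect gives no bias. The figure of about 30% of couples excluded at an omission rate of 0.1% rests on 360 items per couple, exclusion of the whole couple for one blank, and independent omissions. Under those conditions the rule alone would exceed the 20% attrition allowance; with clustered omissions it would exclude fewer.

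**What to change.** The change concerns the analysis only. It alters neither clinical management nor the right to withdraw.

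- Limit the exclusion criteria to facts known before allocation.
- Move the three events to a section on withdrawal and missing data, where they are recorded as events or reasons.
- State that all randomised couples are analysed in the arm assigned, using all available data, for example with a mixed model or with GEE fitted without a complete-case restriction. Repeated measures ANOVA in its standard form needs every visit.
- Continue to seek the T6 and T7 scales from couples who stop sessions but have not withdrawn consent.
- Report losses by arm and reason.

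The cost is an amendment of one paragraph, resubmitted to the ethics committee as the Protocol amendments section requires, and slightly more analysis work. The enrolment target stays at 62 couples per arm. One loss may be beyond repair: recruitment began in March 2022, so T6 and T7 data may never have been collected from couples already excluded. Those couples should be reported as randomised with missing outcomes.

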## Randomization

After signing the informed consent, participants will be randomly assigned to obstetric wards 2 through 7. To prevent cross-contamination that could impact intervention effectiveness, those in wards 2 to 4 will be assigned to the intervention group, and those in wards 5 to 7 will be part of the control group. The intervention group will receive MBCI in addition to routine psychological care, whereas the control group will only receive routine psychological care.

## Intervention

### Framework of MBCI

The MBCI framework is based on mindfulness attention-acceptance theory, incorporating techniques from Mindfulness-Based Stress Reduction (MBSR) and Mindfulness-Based Childbirth and Parenting (MBCP). It also integrates findings from previous research and literature on the psychology of parents who have experienced TOPFA. Researchers, psychological counselors, and mindfulness trainers have developed a preliminary framework diagram for MBCI (Fig. 3).

**Fig. 3 Fig3:**
[figure not shown]
Framework diagram for MBCI

#### Implementation of MBCI

##### Intervention content

Six mindfulness intervention sessions will be conducted, with themes progressing sequentially. Each session includes four modules: A - Theoretical Explanation; B - Mindfulness Exercises; C - Couples’ Communication and Sharing; D - Homework Assignment. Table 1 details the specific contents.

**Table 1 Tab1:** Content of mindfulness-based for couple-centered intervention

Theme	Content	Homework
Session 1: Embarking on the Journey of Awareness	**Theoretical Explanation**: explaining the origin, connotation, functions, and practice techniques of mindfulness. **Mindfulness Exercises**: ①Mindfulness Breathing: fostering continuous awareness of the present through breathing, cultivating a non-judgmental, open, and accepting mindset. ②Couple’s Birth Fear Communication Exercise: aiming to reduce fear of induced labor and enhance mutual understanding and support. **Communication and Sharing**: couples discuss and share their experiences with the mindfulness exercises.	①Practicing mindfulness breathing once a day ②Conducting a couple’s communication exercise, allowing the couple to choose the topic.
Session 2: Accepting the Reality of Baby Loss	**Theoretical Explanation**: explaining the role and methods of love meditation and farewell, alongside mindfulness yoga. **Mindfulness Exercises**: ①Love Meditation and Farewell: involves sending loving blessings to family and friends, offering blessings to the lost fetus, and bidding farewell inwardly. ②Mindfulness Yoga: pay attention to bodily sensations and emotional changes during stretching exercises, maintaining an open, accepting, and non-judgmental attitude. **Communication and sharing**: same as the previous session.	①Engaging in mindfulness yoga exercise once daily. ②Participating in one couple’s love meditation exercise, expressing gratitude for mutual support and companionship.
Session 3: Awareness of Body and Mind Experience	**Theoretical Explanation**: delving into the meaning and significance of attention in mindfulness. **Mindfulness Exercises**: ①Mindfulness Yoga: same as the previous session. ②Body Scan: sequentially experience and sense body sensations with a non-judgmental, curious, and open attitude. **Communication and sharing**: same as the previous session.	①Engaging in mindfulness yoga exercise once daily. ②Conducting one body scan exercise
Session 4: Self and Partner Acceptance	**Theoretical Explanation**: understanding the meaning and importance of an acceptance attitude in mindfulness. **Mindfulness Exercises**: ①Body Scan: identical to the previous session. ②Couple’s Future Fear Communication Exercise: encourages couples to understand and accept each other’s future fears, fostering mutual support. **Communication and sharing**: identical to the previous session.	①Engaging in one body scan exercise daily. ②Participating in a couple’s communication exercise with topics chosen by the couple.
Session 5: Integrating Mindfulness into Life	**Theoretical Explanation**: explaining the meaning, effects, and methods of informal mindfulness practice. **Mindfulness Exercises**: **①**Mindfulness Yoga: same as the previous session. ②Informal Mindfulness Exercises: using raisin meditation as an example. **Communication and sharing**: same as the previous session.	①Engaging in mindfulness yoga practice once daily. ②Engaging in informal mindfulness practice once daily.
Session 6: Coexisting with Future Stress	**Theoretical Explanation**: summarizing and reviewing the theoretical content from the previous five sessions. **Mindfulness Exercises**: ①Informal Mindfulness Exercises: content identical to the previous session. ②Love Meditation and Farewell: repeats the loving-kindness meditation to bid farewell to this special experience and offer future blessings. **Communication and sharing**: same as the previous session.	①Continuing to practice informal mindfulness. ② Using mindfulness to manage future stress.

## Intervention format

The first two sessions will focus primarily on face-to-face intervention on-site, with online intervention as a supplement, whereas the remaining four sessions will be online. Online interventions will be conducted via the WeChat platform, where mindfulness training audios are available. Participants can practice using these audios.

### Intervention duration

Pregnancy mindfulness interventions typically include 6–8 sessions, with each session lasting 0.5–2 h [26]. This provides a basis for determining the duration of mindfulness intervention in this study. Taking into account the Chinese tradition of 30-day postpartum confinement, the intervention period extends from hospitalization for induced abortion to four weeks postpartum, with sessions lasting 1.5 to 2 h each.

